### Blinding

Blinding is not possible due to the design of the trial. Participant diagnosis is confirmed as part of the inclusion criteria, there are no separate arms of the trial and all participants will wear the device in the same manner. The primary outcome is objectively assessed.

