### Intervention

All participants fulfilling the eligibility criteria and providing consent will wear the CAVA device for up to 30 days. To balance the consequences of delaying BPPV treatment with not being able to identify the nystagmus associated with BPPV, individuals with BPPV will be offered a particle positioning manoeuvre after 4 days of wear. The CAVA algorithm will then diagnose each patient based only on the data recorded from the device. The accuracy of the system will be tested by comparing the CAVA system’s diagnosis with each patient’s known diagnosis. The results of the algorithm work (‘the diagnosis’) will not be available until the end of the trial and will not be made available to clinicians or patients during the trial.

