### Data analysis

The device data will be downloaded by the investigator and securely backed up locally as well as uploaded to the University of East Anglia’s secure research storage for permanent (tape backup) storage. The software will be used to convert the data from its encoded form on the SD card into the waveform samples provided by the device. The signals will then be resegmented into files, each file containing a full calendar day.

To train the algorithms, we require a collection of nystagmus waveform segments collected from a patient each labelled with the underlying diagnosis of the patient’s condition. The nystagmus waveforms from a patient’s data will be gathered by the computational team in two ways. First, by finding the positions of presses of the event marker in the signal and searching around these points for nystagmus-like signals; second by reading the patient’s diary entries and searching for signals at times when they have noted spells of dizziness (of course, these two conditions may often co-occur). Signals in these regions will be carefully assessed for possible evidence of nystagmus and any candidate waveforms will be copied and stored. Any relevant comments by the patient will be copied and stored with the accompanying waveforms. We will also use automatic analysis. We have already developed algorithms that can detect nystagmus-like waveforms with high accuracy and these will be used to both verify any waveforms found by the procedure above and to discover any other nystagmus events that the patient was either unaware of or had not marked.

After confirmation of nystagmus waveforms associated with the three target conditions of the study, algorithms will be built and tested to do automatic diagnosis. The most suitable computational technique for this task is machine learning (ML), sometimes known as ‘AI’. When using ML to make classifications, we aim to make maximum use of the available labelled data without falling into the trap of testing on material that is either part of the training set or is correlated with it which could lead to optimistically biased results. Hence the paradigm used here is to train on all the data except for that from a single subject and then test on that subject’s data. This procedure is repeated for each subject in turn and the average error rate and its SD are estimated. This technique is known as cross-validation.

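### The Blinding section rules out all masking for reasons that do not apply to the staff who read the waveforms, and the test input for the held-out participant is not defined

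*Protocol article*

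**What the plan says.** All references are to the protocol article.

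- **Blinding.** "Blinding is not possible due to the design of the trial". The reasons given are that the diagnosis is confirmed at inclusion and that "there are no separate arms of the trial and all participants will wear the device in the same manner". The section adds: "The primary outcome is objectively assessed".
- **Intervention.** "The CAVA algorithm will then diagnose each patient based only on the data recorded from the device". Accuracy is judged by "comparing the CAVA system’s diagnosis with each patient’s known diagnosis".
- **Data analysis.** "The nystagmus waveforms from a patient’s data will be gathered by the computational team in two ways". The first is "finding the positions of presses of the event marker in the signal and searching around these points for nystagmus-like signals". The second is reading "diary entries and searching for signals at times when they have noted spells of dizziness". The team assesses the signals found there, stores the candidates and keeps relevant patient comments with them. Existing detection algorithms are then used to verify these waveforms and to find events the patient did not mark. Each training segment carries the patient's diagnosis. Testing leaves out one participant at a time.
- **Retention.** The device data analysis team confirms who has a qualifying event. Recruitment runs until 255 are confirmed or 400 have been recruited.

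**The concern.** In a diagnostic accuracy study, whoever prepares the input to the index test should not know the reference diagnosis. Here the reference is the known clinical diagnosis, and part of the input may be prepared by people who search and judge signals. The Introduction lists features expected to separate the three conditions, among them nystagmus duration, change of direction and provocation by motion. A reader who knows the diagnosis therefore knows which pattern to expect.

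Two things are at stake. Knowledge of the diagnosis could influence which segments are kept or which participants count as having a qualifying event. Separately, diary help in locating an attack could make the system look better than it would when working from its own recording.

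**Working it through.** The plan gives no figure for this point, so the check is mainly a comparison of sections.

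**Step 1. Do the stated reasons cover every role?**

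| Role | Known diagnosis at entry | No arms, same wear | Can be masked? |
|---|---|---|---|
| Participant | prevents masking | nothing to conceal | No |
| Recruiting clinician | prevents masking | nothing to conceal | No |
| Staff selecting waveforms | does not prevent it | not relevant | Yes |
| Staff confirming qualifying events | does not prevent it | not relevant | Yes |

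The section on the CAVA device says that data are analysed off-line after wear, so the diagnosis can be withheld while signals are read and added afterwards. The blanket statement is wider than its reasons.

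**Step 2. Where does human judgement enter?** Of the three routes to a waveform, event-marker presses are recorded on the device and automatic detection runs on the device signal. Diary entries are not device data. Human assessment of candidates follows the marker and diary searches. A further judgement decides who has a qualifying event. If the cap of 400 is reached with exactly 255 confirmed, 400 − 255 = 145 recruits fall outside the confirmed set and 255/400 = 63.75% are in it.

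**Step 3. What is the held-out participant's input?** Two readings are possible.

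- *Reading A:* the detector and classifier run on the held-out participant's device record. This agrees with the Intervention section.
- *Reading B:* the classifier runs on that participant's gathered segments, some located by diary and judged by staff. This conflicts with the Intervention section.

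The article says only that testing uses the held-out participant's data. Reading B is the more likely, because building and testing follow confirmation of the waveforms and no other test input is described, but it is not stated. Leaving a participant out prevents training on that participant. It does not prevent knowledge of the diagnosis from shaping the choice of that participant's own segments.

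**Step 4. How large could the effect be?** The documents supply no input for this. Two illustrations, resting wholly on assumed values, show only how such a bias behaves.

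*(a) Selection informed by the diagnosis.* Assume true sensitivity of 90%, and that a share s of would-be errors drops out at selection as having no qualifying attack. Apparent sensitivity = 90 / (90 + 10(1 − s)).

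- s = 0: 90/100 = 90.0%
- s = 0.25: 90/97.5 = 92.3%
- s = 0.5: 90/95 = 94.7%

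*(b) Diary help.* Assume 95% accuracy when a segment is found, and that the device alone finds one in a share q of those tested. Overall accuracy = 0.95q + (1 − q)a, with a = 0 (a missed patient counts as wrong) or a = 1/3 (a guess among three).

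- q = 1: 95%, no loss
- q = 0.95: 90.25% to 91.9%
- q = 0.90: 85.5% to 88.8%
- q = 0.80: 76.0% to 82.7%

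**The case against.** The strongest reply is that a reader might infer more than the text says.

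- **That the selecting team is unmasked.** No section says that staff see the diagnosis while selecting, or when the label is attached. It is a fair inference from the blanket blinding statement and the labelled segments, but only an inference. The full clinical investigation plan, the data validation plan or the SAP may deal with it. This stands as a limit on the claim. It does not rescue the Blinding section, which does more than stay silent: it says that masking is not possible.
- **That waveforms are simply hand-picked from diaries.** This is wrong. Event-marker presses are a second source, automatic detectors verify and supplement the search, and storing any candidate is an inclusive rule. Nothing describes discarding atypical waveforms.
- **That Data analysis flatly contradicts Intervention.** Manual gathering is introduced as a step for training, and a segment located by diary is still device-recorded signal. Diary-assisted training and device-only testing can coexist, so the conflict is conditional on Reading B.
- **That the claim of objectivity is shown to be false.** It refers to the primary outcome, which the Outcomes section defines as nystagmus identification, not the three-way diagnosis. It still sits uneasily with the only process described for confirming nystagmus, which includes human assessment.

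A practical objection also stands: Data analysis plans periodic diagnosis tests during the trial, and these need labelled segments. A single lock at the end would block them, so the lock must be per participant.

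**Conclusion.** The point holds in limited form. The Blinding section excludes masking for everyone on grounds that do not apply to those who select waveforms or confirm qualifying events. Data analysis leaves the held-out participant's input undefined. Followed as written, the plan allows knowledge of the diagnosis and diary information to enter the test input.

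If it does, the reported accuracy may be biased, probably upward. This rests on two assumptions: that selectors can see the diagnosis or the diary text, and that the held-out participant is tested on the gathered segments. The documents confirm neither. They therefore do not support the stronger conclusion that the reported accuracy will not be the system's accuracy. The size cannot be computed from them, and the illustrated percentages are not estimates for this trial.

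**What to change.** 1. **Blinding:** limit the statement to participants and clinicians. Add that waveform selection and confirmation of qualifying events are done masked to diagnosis and diary free text, and that the diagnosis label is merged once that participant's segments are locked. Locking per participant lets the periodic tests continue. Hold patient comments back until the lock.
2. **Data analysis:** define the test input. For the accuracy result, score each held-out participant by automatic detection plus the classifier on the device record alone, with event-marker presses allowed because they are device data. Report the diary-assisted result as secondary.
3. **Intervention:** keep the device-only sentence, which would then describe the analysis correctly.

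**Cost.** No additional staff are needed, but the diagnosis and diary text must be withheld until each lock, which means slightly more data handling. Accuracy may look lower. Recruitment began in February 2023, so some segments may already have been labelled and cannot be reselected masked by the same readers. Automatic rescoring can cover these, because the device files are backed up and stored permanently.

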### Intervention

All participants fulfilling the eligibility criteria and providing consent will wear the CAVA device for up to 30 days. To balance the consequences of delaying BPPV treatment with not being able to identify the nystagmus associated with BPPV, individuals with BPPV will be offered a particle positioning manoeuvre after 4 days of wear. The CAVA algorithm will then diagnose each patient based only on the data recorded from the device. The accuracy of the system will be tested by comparing the CAVA system’s diagnosis with each patient’s known diagnosis. The results of the algorithm work (‘the diagnosis’) will not be available until the end of the trial and will not be made available to clinicians or patients during the trial.

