The relationship between balance and eye movements known as the vestibulo-ocular reflex stabilises images on the retina during head movement. When a malfunction occurs in the pathway involving the ears, eyes and brain, an abnormal eye movement is produced, known as nystagmus.^7^ This is characterised by drifting of the eyes in one direction followed by a corrective rapid flick of the eyes in the opposite direction. Different diseases produce different patterns of nystagmus, for example, predominantly horizontal (peripheral vestibular nystagmus), predominantly torsional (BPPV), predominantly vertical (causes outside the peripheral vestibular system).^8^,^10^ The ability to characterise nystagmus will allow us to differentiate between the various vestibular causes of a ‘dizzy attack’ and in the future may provide insights into mechanisms underlying other disorders.

CAVA (continuous ambulatory vestibular assessment) is a wearable device developed to detect nystagmus. As some dizziness can be provoked by the movement of the head,^11^ the CAVA device also records the movement of the head in three axes. The eye movement data captured by the CAVA device is a critical parameter for assessing patients with dizziness.

The CAVA system was evaluated during a clinical investigation involving 17 healthy volunteers. Algorithms were developed to detect physiologically induced nystagmus and achieved an extremely high degree of sensitivity and specificity.^12^ The device was technically reliable, patients were happy to wear it and it was safe.^13^ Participants found the device to be easy to apply and remove and found it to be comfortable to wear. They had little difficulty sleeping while wearing the device and reported that it did not interfere greatly with their daily activities. They did not feel self-conscious wearing the device. From the initial proof-of-concept prototypes, the CAVA device was designed and confirmed to record maximum ocular excursions and eye movements as small as 5 degrees. These tests took place on several subjects with different head shapes, ensuring that recording was not limited by physiological differences or by placement on the face.

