### The CAVA device

The CAVA system will eventually consist of two separate elements: Hardware and software. The software will be developed from the data collected from this trial and is not fully developed or under test in this trial.

The hardware is composed of two parts. First, there is a reusable device that sits over the ear and records eye and head movements; this is comprised of a logging module containing a battery, microcontroller, accelerometer, data storage facility, an event marker button and connection ports. Second, there are two single-use sensory arrays (electrodes) that adhere to the participant’s face (figure 1).The software will consist of a computer algorithm which will compute head and eye data recorded during a 30-day period. The data used to undertake this work will be uploaded onto a computer from an SD card stored in the device. This data analysis is performed ‘off-line’ after the participant has worn the device.

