#### Secondary outcomes

Secondary outcomes include safety events, device compliance, health economics, commercialisation, average time to first dizzy attack, patient acceptability and device malfunctions.

Device compliance will be calculated for each participant by appraising the percentage of time the device was worn for each day of the trial as well as for the entire 30-day trial. Data will be collated to calculate an overall value for device compliance for all participants.

The health economic study will inform the market access plan which will be produced after the study detailing any of CAVA’s financial and other patient benefits to inform the route to its commercialisation. This will be developed using study outputs as well as data from consultation with stakeholders regarding the feasibility of adoption within the NHS, patient and public (PPI) meetings and public dissemination events.

Patient acceptability will be assessed through the use of a bespoke questionnaire, completed by participants at the end of their time in the trial.

Device malfunctions will be recorded, both participant-reported (and perceived) and those noted by the clinical or data analysis teams.

Safety events (adverse events) will be reported by participants and recorded throughout the trial.

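### Only BPPV participants are offered a manoeuvre during recording, and no rule is stated for BPPV data at or after it, so accuracy and time to first attack can be confounded with condition

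*Protocol article*

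**What the plan says.** The Intervention section of the protocol article sets one step that differs by condition: "individuals with BPPV will be offered a particle positioning manoeuvre after 4 days of wear". The reason given is a trade-off between delaying treatment and failing to capture BPPV nystagmus. Participants in all three conditions "will wear the CAVA device for up to 30 days". The same section continues: "The CAVA algorithm will then diagnose each patient based only on the data recorded from the device". The section on the CAVA device describes the software as "a computer algorithm which will compute head and eye data recorded during a 30-day period".

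The Data analysis section narrows what the algorithm receives: "To train the algorithms, we require a collection of nystagmus waveform segments collected from a patient each labelled with the underlying diagnosis". Segments are found around event-marker presses and diary entries. Automatic detection is used as well, to "discover any other nystagmus events that the patient was either unaware of or had not marked". Testing leaves out one subject at a time.

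The Introduction states that "the CAVA device also records the movement of the head in three axes" and lists motion-provoked nystagmus among five discriminating parameters. Secondary outcomes include "average time to first dizzy attack". Under Retention, recruitment runs until 255 participants have a qualifying event or 400 have been recruited.

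**The concern.** The manoeuvre follows from the reference diagnosis, so any trace it leaves in a recording follows from the label. A future patient without a diagnosis would carry no such trace, and accuracy gained from it would not transfer to the intended use.

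There are three routes:

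- **Training and testing.** Nystagmus and head movement recorded during the manoeuvre could be picked up by the search and stored as BPPV examples. This could raise BPPV sensitivity. It could also raise specificity for the other two conditions, because fewer BPPV participants would be assigned to them.
- **Qualifying events.** A segment provoked by the manoeuvre could count as the event that makes a participant evaluable, and so count towards the recruitment target.
- **Time to first attack.** Participants without an attack are censored when the device is returned. In BPPV the attack risk may also change at the manoeuvre. A simple average compares the conditions on unequal terms.

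**Working it through.** **Accuracy: the passages side by side**

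1. The manoeuvre is offered in one class only, after day 4 (Intervention). Up to 26 of 30 wear days (26/30 = 87%) can therefore follow it, in BPPV alone.
2. The electrodes are meant for 23 hours of wear a day (The CAVA device). Unless the device is taken off for the visit, the manoeuvre would be recorded. The article does not say which applies.
3. The search for segments has no stated end point and is not limited to what the patient marked (Data analysis).
4. Leave-one-subject-out testing stops a participant's own data from being used for both training and testing. It does not protect against a feature shared by a whole class: the held-out BPPV participant carries it, and so do the BPPV participants in the training set.
5. The size of the effect would need the share who accept the manoeuvre, the share wearing the device during it, and the number of segments it yields. None is given, so no figure can be derived.

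**Time to first attack: an illustration**

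The plan gives no figure of its own to reproduce. The inputs are at least 2 episodes in the 4 weeks before consent (Population), a 30-day limit and day 4 (Intervention). Assumptions: a constant rate *r* per day, a range of 2 to 28 attacks per 28 days, and between 0% and 100% of BPPV participants free of attacks after the manoeuvre.

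Formulas, for a window of *T* days:

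- Share with no attack by day *T*: exp(−*rT*)
- True mean: 1/*r*
- Mean among those with an attack: 1/*r* − *T* exp(−*rT*) / (1 − exp(−*rT*))

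At 2 per 28 days, *r* = 2/28 and 1/*r* = 14 days:

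- No attack by day 4: exp(−8/28) = 0.751, so about 25% have had one (about 21 of 85).
- No attack by day 30: exp(−60/28) = 0.117, so 88% have had one.
- Mean among those with an attack, 30-day window: 14 − 30 × 0.117/0.883 = 10.0 days.
- The same with a 4-day window: 14 − 4 × 0.751/0.249 = 1.9 days. This is the extreme in which no BPPV attack follows the manoeuvre.

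| Attacks per 28 days | True mean (days) | No attack by day 4 | Mean if attacked, 30 days | Mean if attacked, none after day 4 |
|---|---|---|---|---|
| 2 | 14 | 75% | 10.0 | 1.9 |
| 7 | 4 | 37% | 4.0 | 1.7 |
| 28 | 1 | 2% | 1.0 | 0.9 |

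The direction depends on the estimator. Take the mean time without attack restricted to 30 days, at 2 per 28 days. Without any effect of the manoeuvre it is 14 × 0.883 = 12.4 days. With no attacks after day 4 it is 14 × 0.249 + 0.751 × 26 = 23.0 days. So the mean among those with an attack falls while the restricted mean rises.

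**The case against.** The strongest objection is that the article condenses a fuller investigation plan and defers detail to a data validation plan and a statistical analysis plan, neither of which is shown. Cut-offs and censoring rules may stand there. This is fair, and it limits the point: no error in the final analysis is shown. What remains is that the article itself states the condition-specific step, the common window, the open search and the average.

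Several stronger readings are tempting but not supported:

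- **That all recorded data go into the algorithm.** The Data analysis section describes selected, assessed segments. Attack-free time yields no segments, and no passage proposes recording length, day of wear or event count as inputs.
- **That BPPV recordings contain the manoeuvre.** It is offered, not compulsory, and wear during it is not stated. If the device is off, the main route closes for the manoeuvre itself. That the manoeuvre provokes nystagmus in these participants is also an assumption; the Introduction mentions symptom provocation only where the diagnosis is wrong.
- **That 255 of 400 is an attack rate.** The 400 is a ceiling on recruitment and also allows for participants who do not wear the device.
- **That time to attack is necessarily biased low, most of all in BPPV.** The article does not say how the average is formed, and the direction changes with the estimator. First attacks before the manoeuvre are unaffected. Nor does the article say that this outcome will decide how long the device must be worn.

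The objection on cost also stands. Barring every BPPV event after the manoeuvre from qualifying status would be expensive. At 2 attacks per 28 days, 85/0.249 is about 340 BPPV participants, against a ceiling of 400 for all three conditions.

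**Conclusion.** The point holds in a limited, conditional form. The article gives one class a label-driven step during recording and states no rule for data at or after it. If the device is worn during the manoeuvre, diagnostic accuracy and the qualifying-event count can be inflated, and the validation scheme would not reveal it. The amount cannot be computed from the document.

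For time to first attack, censoring is to be expected, since the Retention section anticipates participants without an attack. On the constant-rate assumption, the mean among those with an attack understates a true mean of 14 days by about 4 days at the minimum entry rate, even without any manoeuvre, and by almost nothing at daily attacks. The added effect of the manoeuvre in BPPV depends on uptake, effect and estimator, none of which is given.

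This is a worthwhile, low-cost improvement to the analysis rules. It does not show that the results will be wrong, and it does not question the timing of the manoeuvre.

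**What to change.** Leave patient care as it is, and fix these rules before the data are analysed:

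1. Record the date and time of the manoeuvre. Exclude segments recorded during that visit from training, testing and qualifying-event status.
2. Add two sensitivity analyses of accuracy: one using only pre-manoeuvre data in BPPV, and one using days 1 to 4 in all three conditions. Do not change the recruitment target for either.
3. Report time to first attack by condition with a Kaplan-Meier estimate, censored at device return and, in BPPV, at the manoeuvre.

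The cost is one date-and-time field, some text in the analysis plan and slightly fewer BPPV segments. If the device proves to be off during the manoeuvre, the first rule removes little or nothing. The sensitivity analyses will have wide intervals: at the minimum entry rate only about 25% of participants, roughly 21 of 85 per condition, have an attack by day 4. For the same reason the BPPV Kaplan-Meier curve may not reach its median, because after day 4 it rests on those who decline the manoeuvre or have it later.
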